### Procedure for unblinding if needed {17b}

Not applicable.

## Data collection and management

### Plans for assessment and collection of outcomes {18a}

Enrolled participants will complete the dizziness handicap inventory survey to obtain baseline dizziness disability. Participants will be asked to complete weekly surveys for 4 weeks to measure dizziness handicap over time. The close follow-up will protect against loss to follow up. Computerized surveys will be used at follow up to assess patient reported outcomes. Generally, the participants will complete on their own on a computer or smartphone. The participants baseline survey includes the following elements.Dizziness characteristics: Including questions about the type of dizziness, duration, severity, triggers, and associated symptoms.Dizziness handicap inventory: Identifies dizziness disability and includes functional, emotional, and physical elements.Days out of role: self-report measure used by the World Health Organization to quantify the number of days a person was totally unable to carry out usual activities because of a health conditionPatient Health Questionnaire (PHQ)−4Patients will also be asked if a DHT or CRM was performed at or since the ED visit, when it was performed, and who performed it (self, provider, other)

### Plans to promote participant retention and complete follow-up {18b}

We will use various methods to ensure the retention of participants that have been shown to be effective for us in prior trials. At enrollment, the study team collects as much contact information as possible from the subject. We will also make obtaining the outcome information as easy and convenient as possible for subjects. Subjects will have several options for completing the outcome assessment including phone interview, text messaging response, or online survey in either English or Spanish We will send subjects notifications for the outcome assessment using phone calls, emails, and text messages. With careful attention to these additional retention methods, high rates of retention should be as good or better in this project as compared to our prior studies.

### Data management {19}

Research data for eligible patients will be captured electronically via electronic medical records. Additionally, we will obtain data directly from patient questionnaires. We will use a REDCap database to screen and conduct outreach to potentially eligible patients. The REDCap database will be housed within KPSC. The data and safety monitoring plan for this study included monitoring recruitment progress and potential adverse events resulting from data collection and the intervention activities. This research study is staffed by a research support team with a project manager and data manager/programmer to establish and monitor all data management protocols. All data will be abstracted into electronic data files that will use a subject code to identify participants. These subject codes will be linked to patient medical record number and name in a file separate from the data files. Data will be stored on password protected, encrypted environment with user-level access control limited to study personnel. All data transfers are encrypted. Access to any hard copy data will be restricted to internal research team members and stored in locked file cabinets.

### Confidentiality {27}

Breach of confidentiality and risk of psychological distress: We are mindful of the sensitive nature of patient’s medical records and have the utmost concern for the human subjects who will be part of this study and will take steps to ensure protection of confidentiality. Confidentiality of data will be maintained in this study through several standard procedures. Electronic data will be kept in password-protected files on a secure network at KPSC. Subjects will be identified through a unique identification number. This number will be used for all forms related to this study and in the analytic datasets. Thus, the identity of the person providing data cannot be determined from the raw data themselves. A master file containing the names of participants and their unique identifiers will be kept in a password-protected computer file, separate from the analytic files. All research study staff with access to protected health information have been trained in procedures to protect the confidentiality of subject data.

Analytic files will be maintained in a secure, password-protected environment with user-level access control limited to study personnel.

### Plans for collection, laboratory evaluation and storage of biological specimens for genetic or molecular analysis in this trial/future use {33}

We will not collect biological specimens as part of this trial.

## Statistical methods

### Statistical methods for primary and secondary outcomes {20a}

The primary outcome is the dizziness handicap inventory (DHI) which is a continuous (0–100) measure of dizziness disability based on a patient’s responses to 25 survey questions. Higher scores indicate more disability. We will use the Ceballo validated Spanish translation for the Spanish speaking individuals. As a sensitivity analysis, we will substitute 2 Lopez questions because we did not think the Ceballo translation was optimal for the following questions: Does bending over increase your problem? (Ceballo: When you get up, does your problem increase?]-Does turning over in bed increase your problem? (When you get out of bed, does your problem increase?] The DHI outcome will be obtained at 1-week intervals after the ED visit for 4 consecutive weeks—corresponding to 4 assessments. We will obtain 4 weekly assessments as we expect that time to recovery will vary given our heterogenous dizziness population. The primary analysis will be a multi-level model as follows: dependent variable (outcome) is the DHI (continuous); fixed independent variables are ED-level intervention group (0/1), patient intervention group (0/1), an interaction term of ED-level intervention with patient intervention group, patient severity at the time of ED visit (continuous), and assessment number (categorical, 1–4); and including a random ED-level intercept. This method allows us to capture variability in recovery over time while maintaining all of the variation in our continuous outcome. We include the severity at the time of the ED visit measure in the model to adjust for baseline disability, protecting against any random imbalances. Because of the two concurrent interventions (ED-level [0/1], patient-level [0/1]), patients will be in either a no intervention group, an ED-level intervention group only, a patient-level intervention group only, or both an ED- and patient-level intervention group. For a secondary analysis, we will add an interaction term of assessment number and intervention group (i.e., a 3-way interaction term of ED-level intervention, patient-level intervention, and assessment number) to further evaluate if any association of intervention group with the DHI outcome is modified by time to assessment. We will make comparisons of the effectiveness of the intervention at each time interval by estimating average marginal effects from our secondary model and comparing marginal effects using Wald Tests. We do not anticipate that our interventions will have differential effects by sex, either at the patient or provider level. Dizziness presentations in the emergency department are more common in females, although at this point there is little biological understanding of the reason for this. For the patient level analyses, we will disaggregate the data and perform analyses separate for male and female patients to assess for heterogeneity. In secondary analyses, we will explore if patient factors (age, sex, Charlson co-morbidities, health literacy) modify the effect of interventions with the outcome. Health literacy will be measured at the first outcome assessment using the BRIEF health literacy tool, 80 which was selected using the Boston University Health Literacy Tool Shed.

We initially considered performing the analysis using time to event (Cox proportional hazard model) based on a fixed and pre specified percentage improvement in the DHI from baseline. We felt, however, that this approach had two important limitations. First, there is not an established DHI threshold of success to use for time to event, and the appropriate threshold likely varies by condition. Second, a time to event analysis would dichotomize a continuous variable which substantially comprises statistical efficiency, information, and precision (e.g., true difference in degree of DHI improvement), and power [12, 36, 47, 49].

SPIRIT guidance: Statistical methods for analyzing primary and secondary outcomes. The statistical analysis for secondary and exploratory outcomes will be multi-level regression models as with our primary outcomes. For the cost analysis, the inputs will include tests, medications, procedures, consultations, and level of visit. Additional costs will also be gathered relating to hospital admission and subsequent visits to the ED. Unit costs will be derived from nationally representative sources (e.g., Medicare fee schedule). Costs often have a skewed distribution and thus will be log-transformed to achieve a more normal distribution. The costs in patients treated by pre-intervention providers will be compared to costs in patients treated by post-intervention providers using the t-test and also a generalized linear model (GLM). General concepts for modeling costs will be followed. [40, 46] Reference to where other details of the statistical analysis plan can be found, if not in the protocol.

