#### Patient level

##### Initial design

We planned to have 800 patients for analysis of the patient level intervention. We have two concurrent interventions: provider-based intervention (pre-intervention period vs post-intervention period) and patient-based intervention (treatment materials vs standard of care materials). As a result, there will be 4 different groups each with 200 participants: no intervention, provider-based intervention only, patient-based intervention only, both provider- and patient-level interventions. Consistent with 2019 extension of CONSORT guidelines for multi-arm parallel-group trials, [25] our power considerations are based on our two primary comparisons: no intervention vs ED-level intervention,no intervention vs patient-level intervention. To assess power, we consider a clinically meaningful effect size to be a >=15% difference in the DHI outcome between the intervention and control group. In the medical literature, there has been some variation in thresholds of the minimal clinically important change (MIC) for the DHI. In the original derivation of the DHI, an 18-point difference was felt to be the MIC [23]. However, this conclusion was based on standard errors of the difference from test-retest in 14 participants. In a subsequent study of 32 dizziness patients, Tamber et al. found that a change of 11 points (corresponding to a 28% difference) was a strong discriminator of patients who improved by at least 2 points on a global self-report disability measure (the Disability Scale) at 48 h compared with patients who did not improve (c-statistic, 0.83) [51]. Friscia et al. performed a study in 45 dizziness patients and found that an approximately 10% change in the DHI score after 4–6 weeks was strongly associated with the established minimal clinically important difference in the 15-item Global Rating of Change (GROC) scale (c-statistic, 0.80) [14]. In an outpatient clinical trial of an internet-based intervention for vestibular physical therapy and cognitive behavioral coping strategies in patients with chronic dizziness, Geragherty et al. found that the intervention group had a 14% lower DHI compared with the control group [16]. Supporting that the 14% difference is clinically meaningful, 62% of the intervention group reported overall improvement compared with 33% of controls (*p*<0.001) [16]. For DIZZTINCT-2, we concluded that it was best to ensure that we have power to detect the lower range of a minimal clinically important difference between groups (i.e., 15%) for two main reasons: (1) Given that our interventions are low risk, scalable and applicable to a large target population, even a relatively small effect size would likely justify wide implementation and (2) If our intervention also improves the efficiency of care, then even a very small improvement in clinical outcomes would also justify wide implementation.

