#### Patient level

Participants will be randomized individually, stratified by site, sex and age, to either the usual care (control) or enhance usual care (intervention) arms using a random number generator. Twenty-five percent of enrolled participants will be assigned to each of the 4 arms. The allocations were generated in randomly permuted block sizes for each of the strata, to limit the possibility of study staff being able to predict the next assignment. Based on the time and hospital they present to for their dizziness care, the site may or may not have received the intervention.

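### The primary DHI model leaves out sex and age, two of the three factors that stratify the individual randomisation

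*Protocol article*

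**What the plan says.** Sequence generation {16a}, Patient level: "Participants will be randomized individually, stratified by site, sex and age". The Trial design section names the same three factors.

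Statistical methods {20a} gives the primary model term by term. After the two 0/1 intervention indicators it lists "an interaction term of ED-level intervention with patient intervention group, patient severity at the time of ED visit (continuous"). From the severity term to the end, the list reads "patient severity at the time of ED visit (continuous), and assessment number (categorical, 1–4); and including a random ED-level intercept". Sex and age are not in that list. Later in the section they appear only in analyses run separately for men and women and in an exploratory look at effect modification.

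Statistical methods {20a} does not say which coefficient or contrast is the primary patient-level test. Sample size {14}, Initial design, does: "our power considerations are based on our two primary comparisons: no intervention vs ED-level intervention,no intervention vs patient-level intervention". The same section states that "there will be 4 different groups each with 200 participants", and the power table for the patient-level intervention is built on 200 against 200.

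On baseline, Plans for assessment {18a} says: "Enrolled participants will complete the dizziness handicap inventory survey to obtain baseline dizziness disability". Statistical methods {20a} says that the severity measure is in the model to adjust for baseline disability, without naming the instrument.

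**The concern.** When allocation is balanced within strata, differences between strata cancel out of the treatment comparison. A model that ignores the strata still counts those differences as residual noise. Its standard error is then larger than the design warrants, and confidence intervals and tests are conservative. Both factors are known for every randomised participant, so the loss buys nothing.

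A second, weaker point concerns the contrast. With 0/1 coding and a product term, the patient-group coefficient is the effect where the ED intervention is absent. That matches the declared comparison with the no-intervention group. Participants are also randomised to the patient materials after the ED intervention has started, and those two cells do not enter the declared comparison. The Sample size revised section reports a DHI standard deviation above the planning value and expects most benefit in groups that may be only 20% of the cohort, so precision matters.

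**Working it through.** **Strata against model terms**

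| Stratifier | In the primary model? |
|---|---|
| Site | Yes, as the random ED intercept |
| Sex | No |
| Age | No |

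Let R² be the share of the remaining DHI variance (after severity, assessment and site) that sex and age explain. Other things equal, the standard error without them is about 1/√(1 − R²) times the standard error with them. The article gives no R² and no correlation of sex or age with DHI, so no figure can be put in. The direction is known; the size is not.

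**The plan's own power figure**

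Inputs from Sample size {14}: means 42 and 35.7 (difference 6.3), SD 16, 200 per group, alpha 0.05 (two-sided assumed), ICC 1.9%. The stated results are power 0.97 and 113 per group for power 0.80.

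- Without clustering: SE = 16 × √(2/200) = 1.600, and 6.3/1.600 = 3.94, so power is 0.976. This agrees with 0.97, but the n for power 0.80 is then 102.
- With design effect 1 + (200/15 − 1) × 0.019 = 1.234: power is 0.943, and the n for power 0.80 is 114 (stated 113).

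No single variant gives both stated figures, but each is matched by one of them. The declared contrast is therefore the one that was powered.

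**Simple contrast against phase-averaged contrast** (one DHI value per participant, no clustering, n per cell)

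- Simple, pre-intervention cells only: variance 2σ²/n. With σ = 16 and n = 200, SE = 1.600.
- Averaged over both phases, b_patient + 0.5 × b_interaction from the same model: variance σ²/n, SE = 16/√200 = 1.131.
- Variance ratio: 2.00.

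If a share p of participants is pre-intervention, the ratio of simple to equally weighted averaged variance is 4(1 − p). With N = 800 and assumed shares:

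| p | SE simple | SE averaged | Variance ratio |
|---|---|---|---|
| 0.3 | 2.066 | 1.234 | 2.8 |
| 0.5 | 1.600 | 1.131 | 2.0 |
| 0.7 | 1.352 | 1.234 | 1.2 |

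Power for 6.3 points, equal cells, equal effect in both phases. The SDs of 20 and 24 are assumptions, because the article says only that the SD was higher than expected:

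| SD | N = 800: simple / averaged | N = 1500: simple / averaged |
|---|---|---|
| 16 | 0.976 / >0.999 | >0.999 / >0.999 |
| 20 | 0.883 / 0.994 | 0.991 / >0.999 |
| 24 | 0.747 / 0.960 | 0.949 / 0.999 |

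**If the effect differs by phase.** Let r be the post-phase effect divided by the pre-phase effect. With equal cells, the averaged test statistic is √2 × (1 + r)/2 times the simple one.

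- r = 1: 1.41
- r = 0.5: 1.06
- r = √2 − 1 = 0.41: 1.00, and below that the averaged contrast has less power.

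**The case against.** The simple contrast is a declared choice. The article treats the design as multi-arm, names two comparisons with the no-intervention group, and powers the patient-level one at 0.97. Choosing between a simple and an averaged effect is a choice of estimand. The two phases may also differ: Objective 1 includes patient-oriented resources in the ED-level strategy itself, so post-phase controls may already receive overlapping content. All of this stands, and it is why the averaged contrast is offered only as an addition.

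A reader might infer that the interaction term throws away half the data. It does not, because the averaged contrast from that same model has SE 1.131. The difference comes from which contrast is declared.

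A reader might also infer that the trial is underpowered. The documents do not support that. At the planned SD, power is adequate, and at the expected total of about 1500 it is still about 0.95 for 6.3 points at an assumed SD of 24 with equal cells.

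Nor can one say that baseline DHI is left out. The stated purpose of the severity covariate makes baseline DHI its natural reading, so only the wording needs settling.

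On the strata, it can be said that site is covered, that inference is only conservative, and that sex and age are examined elsewhere. The first two are true and limit the weight of the point. The third does not help, since separate and exploratory analyses leave the primary standard error unchanged. The statistical analysis plan is not shown and may add the terms, but the article prints a full list without them.

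**Conclusion.** The point holds as a modest efficiency weakness. The primary model as listed omits two of the three randomisation strata. The estimate is not biased, and the false-positive rate is not raised by this omission. The model-based standard error of the patient-level effect tends to be somewhat too large, by an amount that the documents do not allow to be computed.

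The contrast is a secondary suggestion. The halved variance rests on equal cells ("Twenty-five percent of enrolled participants will be assigned to each of the 4 arms", although the pre/post split will follow calendar recruitment) and on equal effects in both phases. If the post-phase effect is half the pre-phase effect, the gain in the test statistic is only about 6%, and below a ratio of about 0.41 it becomes a loss.

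**What to change.** 1. Add sex and the age stratum, as used in the randomisation, to the fixed effects of the primary DHI model. If the analysis plan already does this, bring the two descriptions into line.
2. State whether the severity covariate is the baseline DHI.
3. Optional: keep the declared comparison and also report, from the same model, the patient-level contrast averaged over both ED phases. Show the phase-specific effects and the interaction beside it, and say that the average assumes broadly similar effects in the two phases.

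The cost is wording and a few lines of code, since the stratifiers are recorded at randomisation. Timing matters: Trial status reports that enrolment has ended, and the blinding section says that the analysts are not blinded. The change should be dated before any between-arm analysis of DHI. If that is no longer possible, the adjusted model and the averaged contrast should be reported as supplementary.

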
For our power calculation, we expect the baseline DHI in these acute ED dizziness presentations to be approximately 60 [2, 17, 18, 22, 24, 34, 37, 48, 52]. In the short-term follow-up period, we expect the non-intervention groups to improve by approximately 30% [6, 52], corresponding to a mean outcome DHI of 42. We consider the MIC for the intervention groups compared with the control group to be 15%, corresponding to a mean outcome DHI of 35.7. A more than 15% difference will exceed Jacobson’s original threshold of change in baseline of 18 points for the intervention group,70 and also differ from the control group by the ~10% threshold identified by Friscia et al as an MIC [14]. Based on the medical literature, we expect the standard deviation (SD) of DHI outcomes in our population will be 20–50% of the mean [18, 37, 52]. For our power calculation, we use a SD of 16 which is the high end of the estimate.

To calculate power for the patient-level intervention, we used two-sample means test and adjusted the estimate considering the effective sample size accounting for the ICC of the ED-facility that we found in DIZZTINCT-1 (1.9%). For this comparison, we have a power of 0.97 to detect a 15% difference in DHI outcome (35.7 vs 42) with our target sample size of 200 per group (Table 2). To achieve a power of 0.80, we would only need 113 patients per group. If larger differences in the intervention and control groups are obtained, then our power increases accordingly.

**Table 2 Tab2:** Power calculations for patient-level intervention differences in dizziness handicap inventory outcome in intervention vs control population

Control, mean outcome (DHI*)	Intervention, mean outcome (DHI*)	Outcome difference b/t treated and control	SD	Alpha	ICC**	Power for 400 subjects (200 per group)	Minimum sample size for power >0.8
42	31.5	25% better	16	0.05	1.9%	1.0	96 (48 per group)
42	33.6	20% better	16	0.05	1.9%	0.99	136 (68 per group)
42	35.7	15% better	16	0.05	1.9%	0.97	226 (113 per group)
30	25.5	15% better	12	0.05	1.9%	0.95	246 (123 per group)
20	17	15% better	8	0.05	1.9%	0.95	246 (123 per group)

Shaded row indicates the power calculation for the prespecified threshold of a 15% difference between intervention and control groups. Calculations made using two sample means test accounting for ICC of 1.9%

**DHI* dizziness handicap inventory

***ICC* intraclass correlation coefficient

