### Methods in analysis to handle protocol non-adherence and any statistical methods to handle missing data {20c}

Many participants will not complete all 4 surveys; however, the longitudinal models planned for the primary analyses above should account for this. When appropriate, multiple imputation will be used. Exploratory analyses may focus on how many physicians at a site used the CME intervention and if possible, we will conduct analyses evaluating the primary outcome within the subset of physicians who viewed the CME.

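### The primary DHI model is written with a random intercept for ED only, so a participant's repeated weekly scores count as independent and the standard errors of both intervention effects are too small

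*Protocol article*

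**What the plan says.** In the protocol article, section {20a} (Statistical methods for primary and secondary outcomes) introduces the model with "The primary analysis will be a multi-level model as follows: dependent variable (outcome) is the DHI (continuous" and then goes through its terms. The fixed effects are ED-level intervention, patient-level intervention, their interaction, severity at the ED visit and week of assessment. The list ends "and assessment number (categorical, 1–4); and including a random ED-level intercept". The data are repeated measures: "The DHI outcome will be obtained at 1-week intervals after the ED visit for 4 consecutive weeks—corresponding to 4 assessments".

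The secondary model adds a three-way interaction to this one. The same section says that secondary and exploratory outcomes will be analysed by multi-level regression in the same way as the primary outcomes.

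On missing surveys, section {20c} says: "Many participants will not complete all 4 surveys; however, the longitudinal models planned for the primary analyses above should account for this". It continues: "When appropriate, multiple imputation will be used".

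The article names no participant-level random effect, residual covariance structure, GEE or robust variance. It gives no within-person correlation of the DHI.

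**The concern.** A participant's DHI scores one to three weeks apart will be correlated, and adjustment for severity at the ED visit removes only part of that. In the model as written, the ED intercept is the only thing that links scores. The DIZZTINCT-1 facility ICC that the article uses is 1.9%, so the ED intercept can absorb very little of the correlation between scores from the same person.

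Both intervention indicators take one value per participant. Counting four scores as four independent observations therefore overstates the information about both effects. The confidence intervals would be too narrow and the false-positive rate above the nominal 5%.

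The statement about missed surveys rests on the same model. A likelihood analysis handles outcomes missing at random given earlier outcomes because its covariance lets a person's observed weeks inform the missing ones. Without a within-person covariance, this model cannot do that.

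**Working it through.** **The plan's own figure.** Sample size {14} (Initial design) states "a power of 0.97 to detect a 15% difference in DHI outcome (35.7 vs 42) with our target sample size of 200 per group", and on the SD, "we use a SD of 16 which is the high end of the estimate". With one score per person and no ICC adjustment:

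- SE = 16 × √(2/200) = 1.60
- power = Φ(6.3/1.60 − 1.96) = Φ(1.98) = 0.976, close to the stated 0.97.

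With a design effect of 1 + (200/15 − 1) × 0.019 = 1.234 (15 EDs), the effective n is 162 per group and power is 0.943. With the same kind of design effect, the minimum n for power 0.80 is 114 per group, against the stated 113. So the power calculation uses one score per person and does not depend on the repeated-measures model.

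**Inputs for the check.**
- k, scores per participant: up to 4 ({20a}), with many participants expected to have fewer ({20c}).
- ρ, the correlation between two scores of one participant after covariates and ED: not in the article. Assumed range 0.3 to 0.8.
- Nominal two-sided α of 0.05.

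**Formula.** For a covariate that is constant within a participant, with exchangeable correlation ρ:

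- variance inflation VIF = 1 + (k − 1)ρ
- true SE / reported SE = √VIF
- shortfall of the reported SE = 1 − 1/√VIF
- actual type I error = 2Φ(−1.96/√VIF)

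| k | ρ | VIF | True/reported SE | Reported SE too small by | Type I error |
|---|---|---|---|---|---|
| 4 | 0.3 | 1.9 | 1.38 | 27% | 0.155 |
| 4 | 0.6 | 2.8 | 1.67 | 40% | 0.241 |
| 4 | 0.8 | 3.4 | 1.84 | 46% | 0.288 |
| 3 | 0.3 | 1.6 | 1.26 | 21% | 0.121 |
| 3 | 0.6 | 2.2 | 1.48 | 33% | 0.186 |
| 3 | 0.8 | 2.6 | 1.61 | 38% | 0.224 |
| 2 | 0.3 | 1.3 | 1.14 | 12% | 0.086 |
| 2 | 0.6 | 1.6 | 1.26 | 21% | 0.121 |
| 2 | 0.8 | 1.8 | 1.34 | 25% | 0.144 |

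**In DHI points.** With 200 per group, SD 16, four scores and ρ = 0.6, the reported SE is 16 × √(2/800) = 0.80. The correct SE is 0.80 × 1.67 = 1.34.

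**Simulation of the ED-intercept-only model.** Null trials had 800 participants, 15 EDs, ED ICC 0.019 and four complete scores.
- 150 trials at each of ρ = 0.4, 0.6 and 0.8: the reported SE of the patient-level term was 29%, 37% and 41% too small, and type I error was 0.17, 0.20 and 0.28. The Monte Carlo error is about √(0.2 × 0.8/150) = 0.03.
- A separate run of 200 trials at ρ = 0.6: the patient-level term was rejected in 25% and the ED-level term in 26.5%.

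Both runs agree with the formula within simulation error. The second shows that the ED-level term is affected too.

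**Missed surveys.** Given the fixed effects and the ED, the written model takes a person's week-1 score to say nothing about that person's week-4 score. Missingness that depends on severity at the ED visit is covered, because severity is a covariate. Missingness that depends on earlier follow-up DHI is not. The bias depends on the pattern. In a simulation with drop-out driven by earlier DHI in the same way in both arms, about half lost by week 4 and ρ 0.4–0.8, bias under the null was about zero (at most 0.11 points, within simulation noise). A true difference of 6.3 was estimated as 5.6–6.3. Drop-out that differs by arm could do more harm, but its size was not worked out.

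**The case against.** **The description may be incomplete and the model sound.** The text says that the model includes an ED intercept, which does not strictly exclude other random terms. {20c} calls the models longitudinal, and a separate statistical analysis plan exists that is not shown here. A participant level may be intended. This stands as a possibility and is a good reason to ask. It does not remove the point. The article did not leave the random structure open: it introduced the model as a specification and named one random term. That term alone already makes the model multi-level, so the label does not imply a participant level. The methods sections of the article hand only subgroup plans to the analysis plan. If a participant term is intended, the written model is wrong and should be corrected.

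**A single figure for the error would overreach.** A reader might infer that the standard errors are simply about 40% too small. That value needs ρ = 0.6 and four complete scores. The article supplies no ρ, the relevant ρ is the residual one after adjustment for severity, and many participants are expected to miss surveys. Only a range can be defended.

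**Missed surveys need not bias the result.** A reader might also infer that missed surveys will bias the estimates and that the plan offers nothing against this. Neither follows. {20c} allows multiple imputation, and imputation that uses a person's other weeks could address the gap, although when it applies is not stated. Drop-out that acts alike in both arms produced no bias under the null and at most modest attenuation in the simulation. Imputation alone would not repair the standard errors, because the completed data would still be analysed with no within-person correlation.

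**The sample size is untouched.** This is correct, since the power calculation uses one score per person.

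**Conclusion.** The point holds for the model as written. The reported standard errors of both intervention terms are too small by a factor of √(1+(k−1)ρ). For an assumed residual ρ of 0.3 to 0.8, the shortfall runs from 12% (two scores, ρ = 0.3) to 46% (four scores, ρ = 0.8). Type I error runs from about 0.09 to 0.29 in place of 0.05. Where the trial falls in that range depends on ρ, which the article does not give, and on how many surveys participants complete. The formula assumes equal correlation between any two weeks.

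The missing-data statement in {20c} is not correct for this model when missingness depends on earlier follow-up DHI. Whether that produces material bias depends on the drop-out pattern and on how the imputation provision is used.

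This should be corrected before analysis, because it affects inference on both primary DHI comparisons.

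**What to change.** Add within-participant correlation to the primary model in {20a}, by one of two routes:

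- a participant random intercept nested in ED; or
- an unstructured residual covariance over weeks 1–4 within participant, alongside the ED intercept.

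The second does not assume equal correlation between weeks, and four time points are few enough to support it. Use the same structure in the three-way interaction model and in the secondary outcomes that are measured repeatedly.

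Reword {20c} so that the missing-at-random claim rests on this covariance, and say when multiple imputation will be used and that the imputation model will include a person's other weekly scores. If the analysis plan already has a participant term, bring the article's wording into line with it.

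The cost is a wording change and about one line of model code, with no new data. The confidence intervals will be wider, and correctly so.
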